### Objectives {7}

The primary aim of the iDoT-AFD study is to identify the molecular imaging biomarkers for AFD by analysis of KP metabonomics and multimodal magnetic resonance imaging (MRI). The secondary aim of the iDoT-AFD study is to find out the optimized intervention and the predictive biomarkers of treatment effectiveness in patients with AFD. The third aim of the iDoT-AFD study is to screen out the risk factors and build a clinical early warning model to predict the conversion of AFD to BD.

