### Sample size {14}

The sample size estimation refers to the primary outcome. A clinically relevant medium effect size (*d* = 0.5) is expected to be found in a two-sample *t*-test of at least one of the three interventions compared to TAU when calculating the sample size. Using the power of 1−*β* = 80% and the significance level of *α* = 0.05 (two-sided), 63 participants are needed per group. Considering a drop-out rate of ≤ 30%, 90 participants need to be allocated to each group. Finally, we planned to recruit 120 patients per group for a total of 480 included patients with AFD.

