## Statistical methods

### Statistical methods for primary and secondary outcomes {20a}

To evaluate the effectiveness of the 12-week treatment for patients with AFD, we plan to perform an intention-to-treat analysis to pursue our primary outcome. A mixed-effect model for repeated measures will be applied to analyze the main effects of interventions, time, and the interaction on HAMD total scores to find the optimal treatment for patients with AFD. Covariates like gender, age, education, and the baseline severity of depressive symptoms will be added to the model to correct the potential confounding effects.

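### The tests named for finding the optimal treatment show only that the four arms differ, and the sizing covers only a win over TAU, so neither supports calling the leading arm best

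*Protocol article*

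**What the plan says.** Three places in the protocol article bear on this.

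- **Aim.** Objectives {7} sets the treatment aim, which is the secondary aim of the study: to "find out the optimized intervention and the predictive biomarkers of treatment effectiveness in patients with AFD".
- **Analysis.** Statistical methods {20a} applies a mixed-effect model for repeated measures, by intention to treat and with baseline covariates, to "analyze the main effects of interventions, time, and the interaction on HAMD total scores to find the optimal treatment for patients with AFD".
- **Sizing.** Sample size {14} expects d = 0.5 in a two-sample t-test of "at least one of the three interventions compared to TAU when calculating the sample size". At 80% power and alpha of "0.05 (two-sided), 63 participants are needed per group". After allowing for up to 30% drop-out, "90 participants need to be allocated to each group", and 120 per group are planned.

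Trial design {8} calls the study exploratory, with 1:1:1:1 allocation. The Discussion and Dissemination plans {31a} intend the results as evidence for clinical guidelines.

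**The concern.** Finding the best of four treatments, showing that four treatments are not all equal, and showing that at least one treatment beats a control are three different conclusions. The aim is the first, the tests named in {20a} deliver the second, and the sizing in {14} is for the third. The second and third can both hold comfortably while nothing separates the leading regimen from the next one.

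All three assigned regimens contain an SSRI or SNRI (Intervention description {11a}), so similar results among them are a realistic possibility. Some arm will still rank first. A guideline statement favouring that regimen over the others would then rest on tests that do not compare it with them. This would remain even if TAU were perfectly defined and the comparisons with TAU were corrected for multiplicity.

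**Working it through.** **Inputs.** From Sample size {14}: d = 0.5, two-sided alpha 0.05, power 80%, 63 per group, drop-out up to 30%, 120 planned. Evaluable per arm at the planned enrolment: 120 × (1 − 0.30) = 84. The article gives no expected gap between the active arms.

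**Step 1: reproduce the plan's figure.** n = 2(1.960 + 0.842)² / 0.5² = 62.8, so 63. Inflated: 63 / 0.70 = 90. Both match. (The exact t-test gives 63.8, so 64, an immaterial difference.) Power of a single contrast with TAU at d = 0.5 is 80% at 63 and 90% at 84.

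**Step 2: what the named tests establish.** The null hypothesis for the intervention main effect is that all four means are equal, with 3 degrees of freedom. The interaction's null hypothesis is that the four time courses are parallel. Rejecting either says that some difference exists, not where it lies.

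**Step 3: the case where no active arm is best.** Simplify to one week-12 endpoint with SD 1 and means (0, 0.5, 0.5, 0.5), TAU first. The grand mean is 0.375. The sum of squared deviations is 0.375² + 3 × 0.125² = 0.1875. The noncentrality of the overall F-test is n × 0.1875, which is 11.8 at n = 63 and 15.75 at n = 84. Simulation (200,000 trials) gives:

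| Event | 63 per arm | 84 per arm |
|---|---|---|
| Overall test significant | 83% | 93% |
| At least one arm beats TAU | 95% | 98% |
| Leader beats every other arm, pairwise two-sided 5%, uncorrected | 1.4% | 1.4% |
| Overall test significant, leader not separated | 81% | 91% |

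Each active arm leads in about a third of the trials.

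**Step 4: power if one arm really is best.** Take means (0, 0, 0, 0.5), so that one arm exceeds every other by the plan's own d. The chance that it beats all three others is:

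- 61% at 63 and 78% at 84 with uncorrected pairwise tests;
- about 57% and 74% with Hsu's multiple comparisons with the best at one-sided 5%;
- about 44% and 63% with the same method at one-sided 2.5%.

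**Step 5: smaller gaps (assumption).** With gains over TAU of 0.25, 0.25 and 0.5, the overall test is significant in 64% and 78% of trials, but the leader separates from all others in 14% and 21% (uncorrected).

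**The case against.** The strongest reply is that {20a} is a short statement in a journal article. It names a model from which pairwise estimates follow directly, and it does not exclude contrasts between arms. Which contrasts are tested, and with what adjustment, is ordinary content for an analysis plan that is not shown. That stands: missing contrast detail is not the point. What remains is that the article does state a route to the optimal treatment, and the tests on that route cannot lead there.

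Four stronger readings are tempting but are not supported.

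- **That the 80% is misstated.** Sample size {14} ties it to a comparison with TAU and claims it for nothing else. With equal allocation, any single pair of arms has the same power at d = 0.5.
- **That the arm with the highest mean will be declared the winner.** The article gives no such rule and no definition of optimal. Adverse events and discontinuation, listed in Outcomes {12}, might also inform the choice.
- **That the 1% is a power failure.** In that scenario no arm is best, so rarely separating one is correct behaviour. The figure shows only how little a significant overall test says about the leader.
- **That power for an optimal-arm claim is 14% to 21%.** Those figures depend on an assumed gap that the article does not give.

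The exploratory label and the secondary rank of the aim soften the consequence. The intended use for guidelines keeps it from disappearing. Covariate adjustment would also help: with an assumed baseline correlation of 0.3 to 0.5, the uncorrected 78% at 84 per arm becomes 83% to 91%.

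**Conclusion.** The point holds in limited form. A significant main effect or interaction, or a win over TAU, does not show that the leading arm is better than the other active arms, and {20a} presents those tests as the way to find the optimal treatment. With three equally effective regimens at the plan's d, the overall test is significant in about 83% to 93% of trials with no best arm to find.

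If one arm does exceed every other by d = 0.5, power to show this by Hsu's method at one-sided 5% is about 57% at 63 and 74% at 84 evaluable per arm. It is lower for smaller gaps. These figures assume normal data, one week-12 endpoint and no covariate adjustment. The weakness lies in what may be concluded, not in the arithmetic of the sample size.

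**What to change.** In Statistical methods {20a}, base the treatment conclusion on week-12 contrasts between arms from the same mixed model, with simultaneous intervals. Hsu's multiple comparisons with the best and Tukey's pairwise method are both suitable. Then state the standard:

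- Call an arm optimal only if it is shown better than every other arm.
- Otherwise report the set of arms not distinguishable from the best, and label the ranking descriptive.
- Limit confirmatory wording to superiority over TAU.

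Sample size {14} needs no correction on this point. If a power for the optimal-arm claim is added, compute it for the procedure chosen and state the gap assumed. The uncorrected 61% and 78% should not be printed beside a corrected method.

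The cost is a change of wording and, if wanted, one extra power figure, with no new data or patients. The price is that the trial may often report a set of candidate arms instead of one winner.

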## Methods: participants, interventions, and outcomes

### Study setting {9}

This clinical trial is sponsored by Shanghai Mental Health Centre (SMHC), [name]. Five clinical sites are involved to recruit participants (SMHC, Wuhan Mental Health Center, the Affiliated Brain Hospital of Guangzhou Medical University, Dalian Seventh People’s Hospital, and Xijing Hospital of the Fourth Military Medical University), each with a principal investigator (PI) and a clinical trial coordinator (CTC). The iDoT-AFD study also includes biomedical engineering experts from Shanghai Jiao Tong University and ShanghaiTech University to ensure high-level data mining.

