### Outcomes {12}

The following is the primary outcome:Clinical remission (examiner-rating), defined as total scores less than or equal to 7 on the HAMD-24 at the end of the 12th week

The following are the secondary outcomes:Clinical remission (self-rating), defined as total scores less than or equal to 5 on the QIDS-SR16 at the end of the 12th weekEarly improvement, defined as a ≥ 20% decrease from the baseline HAMD-24 at the end of the 2nd weekTreatment response, defined as a ≥ 50% decrease from the baseline HAMD-24 at the end of the 12th weekSeverity and incidence of adverse eventsThe time of treatment discontinuation for any causeWorking or learning time lost to any cause associated with the present study

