### Assignment of interventions: allocation

#### Sequence generation {16a}

For each center, a randomization list has been made using software-generated randomized numbers by a research assistant without clinical participation in the trial. Randomization is stratified for each clinical site. A block randomization is conducted in an allocation ratio of 1:1:1:1 with a fixed block length per center.

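### Randomisation is stratified by site, but the model description does not name site as a term; if it is left out, tests are likely to be slightly conservative, and naming it costs nothing

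*Protocol article*

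**What the plan says.** Protocol article, Study setting {9}: "Five clinical sites are involved to recruit participants".

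Protocol article, Sequence generation {16a}: "Randomization is stratified for each clinical site", and "A block randomization is conducted in an allocation ratio of 1:1:1:1 with a fixed block length per center". The block length is not given. Site is the only stratification factor mentioned.

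Protocol article, Statistical methods for primary and secondary outcomes {20a}: "A mixed-effect model for repeated measures will be applied to analyze the main effects of interventions, time, and the interaction on HAMD total scores". On adjustment: "Covariates like gender, age, education, and the baseline severity of depressive symptoms will be added to the model". The stated purpose is "to correct the potential confounding effects". Site appears neither as a covariate nor as a random effect, and the stratified design is not mentioned.

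The primary outcome in Outcomes {12} is binary: remission, "defined as total scores less than or equal to 7 on the HAMD-24 at the end of the 12th week".

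**The concern.** Blocking within site balances the arms across sites by design, so differences between sites largely cancel out of the treatment contrast. A model without site does not use this. It counts the between-site variation as residual error, and the reported standard error then exceeds the true sampling variability of the estimate. Confidence intervals are too wide and the test falls below its nominal 5%.

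The article gives some reason to think that sites could differ. HAMD is examiner-rated in an open-label trial, each participant keeps one investigator throughout, the sites lie in five regions of China, and both the usual-treatment arm and the drug classes leave room for local prescribing habits.

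The reason given for the covariates is confounding. In a randomised comparison the stronger reason to include a term is that the allocation was stratified on it or that it predicts outcome. An analysis plan that followed the named list literally would adjust for three demographic variables that were not stratified and omit the one factor that was. At stake is a small amount of power, and agreement between design and analysis.

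**Working it through.** **Inputs from the protocol article.** Five sites; allocation 1:1:1:1 in blocks within site; *d* = 0.5, two-sided alpha 0.05, power 80%; 63 per group, 90 after drop-out of up to 30%; 120 per group planned, 480 in total.

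**Input not in the article.** ρ, the share of outcome variance lying between sites that remains after the listed covariates. Assumed range 2% to 10%.

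**Step 1: reproduce the plan's figure.** n = 2(1.960 + 0.842)² / 0.5² = 62.8, so 63 per group (the exact t calculation gives 64). Drop-out: 63 / 0.70 = 90. Both figures reproduce, and neither depends on site. With 120 recruited, 120 × 0.70 = 84 completers per group.

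**Step 2: effect of adding site.** With total SD 1, the residual SD with site in the model is √(1 − ρ).

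- Standard error without site relative to with site: 1/√(1 − ρ).
- Actual type I error without site under balanced allocation: 2Φ(−1.96/√(1 − ρ)).
- Power with site: Φ(δ/√(1 − ρ) − 1.96), where δ = 0.5 × √(84/2) = 3.240. The reference without site sets ρ = 0 and gives 90.0%.

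| ρ (assumed) | SE ratio | Type I error without site | Power with site | Difference from 90.0% |
|---|---|---|---|---|
| 0.02 | 1.010 | 4.8% | 90.6% | 0.6 points |
| 0.05 | 1.026 | 4.4% | 91.4% | 1.4 points |
| 0.10 | 1.054 | 3.9% | 92.7% | 2.7 points |

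**Step 3: why the last column is an upper figure.** The 90.0% reference treats the estimate itself as carrying the full between-site variance. Under blocked allocation it does not; only its reported standard error does. Power without site is then Φ((3.240 − 1.96)/√(1 − ρ)), which is 90.2%, 90.6% and 91.1%. The loss by this formula is about 0.3, 0.8 and 1.6 points.

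**Step 4: simulation.** Five equal sites, 480 patients, blocks of 4 (assumed), 30% random drop-out, 4,000 runs per ρ, linear week-12 model. The Monte Carlo error on a 5% rate is √(0.05 × 0.95/4000), about 0.3 points.

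| ρ | Mean SE, no site | True SD, no site | Mean SE, with site | Type I, no site / with site | Power, no site / with site |
|---|---|---|---|---|---|
| 0 | 0.1544 | 0.1569 | 0.1547 | 5.3% / 5.4% | 89.0% / 89.1% |
| 0.02 | 0.1545 | 0.1508 | 0.1532 | 4.5% / 4.9% | 90.8% / 90.8% |
| 0.05 | 0.1545 | 0.1510 | 0.1508 | 4.6% / 5.1% | 90.4% / 91.3% |
| 0.10 | 0.1546 | 0.1465 | 0.1467 | 3.8% / 4.8% | 90.9% / 92.6% |

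The direction and rough size agree with the formulas. With no site effect nothing is lost, and at 2% the loss is negligible.

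**Step 5: scope.** All of this concerns a linear model of the HAMD score. It does not carry over directly to a logistic model of remission, where adding site changes the odds ratio as well as its standard error.

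**The case against.** The strongest reply is that the article does not say that site is left out. The covariate list is introduced by *like*, the model is called mixed-effect without its random effects being listed, and this is a condensed article whose full protocol and analysis plan are not shown. That stands. The point can only be conditional, and it amounts to a request to name the term.

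Second, any site effect has to survive adjustment. Baseline severity is in the model, and each participant has the same investigator at baseline and follow-up, so stable differences in rating severity would be partly absorbed. There is also a common manual and training every six months. This stands too: the relevant ρ is the residual share, and it may be small. It does not cover differences between sites in patients' prognosis or in prescribing.

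Third, the error is conservative, and the trial recruits 120 per group where its own calculation asks for 90. That also stands.

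A reader might infer that standard errors *are* too large and precision *is* lost, or that 5% to 10% of the sample (24 to 48 of 480 patients) is wasted. The documents support neither. The first needs both the omission and a prognostic site effect, and the article establishes neither. The second is only an assumed variance share multiplied by 480. It also describes the precision that the model reports: in the simulation at ρ = 0.10 the true sampling SD of the estimate was almost the same without site (0.1465) as with it (0.1452).

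What survives the reply is that the one factor the design stratifies on is not named, while other covariates are.

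**Conclusion.** The point holds as a minor one. Site is the trial's only stratification factor and is not among the covariates that the article names for the HAMD model. If it is left out, and if it predicts outcome beyond those covariates, inference stays valid but is somewhat conservative. Standard errors would be overstated by about 1% to 5.4% for residual between-site shares of 2% to 10%. The power cost at 84 completers per group would be at most about 0.6 to 2.7 points, and nearer 0 to 1.7 points in the simulation. These sizes rest on an assumed variance share, on random drop-out and, in the simulation, on equal sites; the article gives no between-site figure. No conclusion of the trial is put at risk.

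**What to change.** In Statistical methods {20a}, name clinical site (five levels) as a fixed effect in the mixed model, on the ground that randomisation was stratified by it. Include site in the multiple-imputation model described under {20c}, and in whatever analysis is used for week-12 remission.

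For remission, use a site-adjusted risk difference or a site-stratified analysis in preference to a logistic odds ratio, so that adding site does not change the meaning of the effect measure. The average is 480/5 = 96 patients per site, or 24 per arm per site, but recruitment by site is not given. State in advance a rule for pooling sites if any has sparse remission cells.

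The cost is about one line of text and four degrees of freedom. Site is already recorded through the per-site randomisation lists, so no new data are needed. The term should be fixed before outcome data are examined.

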### Interim analyses {21b}

There was no design of any interim analyses because the safety and effectiveness of all four interventions have been proved for patients with MDD in previous studies.

### Methods for additional analyses (e.g., subgroup analyses) {20b}

To explore the potential biomarker identifying AFD, analysis of variance (ANOVA), Kruskal–Wallis tests, or chi-square tests will be applied to compare the group differences of multivariate-dimension information among the first-episode AFD patients, recurrent AFD patients, and patients with BD and HC.

The prediction model of patients with AFD switching from depression to mania or hypomania will be constructed. Multidimensional data obtained at baseline and their changes during the follow-up period will be used to predict the binary outcome (switching to mania/hypomania or not). The concordance index will be calculated to assess the discrimination of the model. Construction of the multivariate prediction model will be conducted by collaborators specializing in biomedical engineering.

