### Eligibility criteria {10}

The inclusion criteria for patients with AFD are as follows: (1) 16–60 years old, (2) meeting the DSM-5 criteria for MDD, (3) scored 20 or higher on the Hamilton’s Depression Scale with 24 items (HAMD-24), (4) enough audiovisual ability and comprehensive ability to accomplish the interview, (5) necessary and appropriate to accept the treatment of antidepressants, (6) scored less than 14 on the Hypomania Symptom Checklist-32 (HCL-32), and (7) meeting DSM-5 specifier for atypical features: mood reactivity and 2 or more of the following—significant weight gain or increase in appetite, hypersomnia, leaden paralysis, and a long-standing pattern of interpersonal rejection sensitivity that results in significant social or occupational impairment.

The exclusion criteria for patients with AFD are as follows: (1) severe medical or neurological problems; (2) previous episodes of mania or hypomania; (3) female patients who are pregnant, planning to be pregnant, or breastfeeding; (4) high risk of suicide; (5) had ECT, MECT, or rTMS in the past 6 months; and (6) experienced severe personality disorder, mental retardation, and anorexia/bulimia nervosa.

Additionally, all included patients with AFD should be drug-naive or medication free for more than 1 week.

The inclusion criteria for patients with BD are as follows: (1) 16–60 years old, (2) meeting the DSM-5 criteria for major depressive episode of bipolar I disorder or bipolar II disorder, (3) scored 20 or higher on the HAMD-24, and (4) enough audiovisual ability and comprehensive ability to accomplish the interview.

The exclusion criteria for patients with BD are as follows: (1) severe medical or neurological problems; (2) female patients who are pregnant, planning to be pregnant, or breastfeeding; (3) high risk of suicide; (4) had electroconvulsive therapy, modified electroconvulsive therapy, or repetitive transcranial magnetic stimulation in the past 6 months; and (5) experienced severe personality disorder, mental retardation, and anorexia/bulimia nervosa.

The inclusion and exclusion criteria for HC are as follows: (1) 16–60 years old, (2) enough audiovisual ability and comprehensive ability to accomplish the interview, and (3) no history of mental disorder or serious somatic disease.

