### Recruitment {15}

The iDoT-AFD study enrolls 480 patients with AFD (120 per treatment group), 100 patients with BD, and 100 healthy participants.

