##### Neuroimaging assessments

Neuroimaging data are acquired using the 3.0-T scanner at available clinical sites. Imaging data including structural MRI, rest state functional MRI, and diffusion tensor imaging (DTI)/diffusion kurtosis imaging (DKI) are collected. All participants are planned to be scanned at baseline, and patients with AFD will also be scanned at 12 weeks, 1 year, and 4 years.

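### The biomarker comparison names ANOVA without an unequal-variance form for groups of very different size; Welch's ANOVA would be a nearly free safeguard

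*Protocol article*

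**What the plan says.** The section on additional analyses {20b} states that "analysis of variance (ANOVA), Kruskal–Wallis tests, or chi-square tests will be applied to compare the group differences of multivariate-dimension information", and that the comparison runs "among the first-episode AFD patients, recurrent AFD patients, and patients with BD and HC". That makes four groups. The Objectives section {7} makes molecular imaging biomarkers of AFD the primary aim.

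The sizes are set under Recruitment {15}: "The iDoT-AFD study enrolls 480 patients with AFD (120 per treatment group), 100 patients with BD, and 100 healthy participants". The split of the 480 into first-episode and recurrent is not given.

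The entry rules under Eligibility criteria {10} differ by group:
- **AFD:** "all included patients with AFD should be drug-naive or medication free for more than 1 week". There is also an HCL-32 ceiling (below 14) and an exclusion for past mania or hypomania.
- **BD:** "meeting the DSM-5 criteria for major depressive episode of bipolar I disorder or bipolar II disorder". No medication condition and no HCL-32 ceiling are listed.
- **HC:** "no history of mental disorder or serious somatic disease".

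**The concern.** The term ANOVA without qualification is usually read as the classical F test, which uses one common error variance for all groups. With similar group sizes, unequal spread does little harm. With one population supplying 480 of 680 participants and two others supplying 100 each, the common variance leans towards the AFD value and is then applied to BD and HC.

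The entry rules give a reason to expect different spread. BD mixes two subtypes and may mix treated and untreated patients. AFD is restricted on medication and on hypomanic symptoms. HC is restricted on psychiatric and serious somatic history. If BD is wider than AFD, markers would be declared too readily against BD. If HC is narrower, real differences from HC would be missed. The issue is one of variance only. It is separate from confounding and would remain if the groups were comparable in mean.

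**Working it through.** **Figures in the article.** The only calculated size is for the randomised comparison: 2 × (1.96 + 0.84)² / 0.5² = 62.7, so 63 per group, and 63 / 0.70 = 90. Both reproduce and neither is affected here. No calculation is given for the biomarker comparison.

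**Inputs.** From the article: 480 AFD, 100 BD, 100 HC, four groups. Assumed because the article does not give them: a 240/240 AFD split, two-sided 5%, normal data, AFD SD = 1 in both AFD groups, and a range of BD and HC SDs. Complete data are also assumed. MRI numbers may be smaller, since "Neuroimaging data are acquired using the 3.0-T scanner at available clinical sites".

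**Pairwise contrast on the pooled ANOVA error (first-episode AFD, n = 240, versus a group of 100).** Write b and h for the BD and HC SDs, and s for the SD of the group being compared.
- Expected pooled variance: M = (239 + 239 + 99b² + 99h²) / 676
- Squared SE used: M × (1/240 + 1/100)
- True squared SE: 1/240 + s²/100
- Rejection rate under equal means: 2 × [1 − Φ(1.96 × SE used / SE true)]

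| Contrast | SD ratio to AFD | M | SE used | SE true | SE used / true | Rejection rate |
|---|---|---|---|---|---|---|
| v BD | 1.00 | 1.000 | 0.119 | 0.119 | 1.00 | 5.0% |
| v BD | 1.25 | 1.082 | 0.124 | 0.141 | 0.88 | 8.4% |
| v BD | 1.50 | 1.183 | 0.129 | 0.163 | 0.79 | 12.0% |
| v BD | 2.00 | 1.439 | 0.143 | 0.210 | 0.68 | 18.3% |
| v HC | 0.70 | 0.925 | 0.114 | 0.095 | 1.20 | 1.8% |

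In each row the group not being compared has SD 1. With a 120/360 split instead (first-episode n = 120), the three BD rates are about 7%, 10% and 15%, and the HC rate is about 2.7%.

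**Overall test, four groups of 240/240/100/100, by simulation under equal means.** Only the BD SD varies. Ranges span independent simulations of 3,000 runs or more.

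| BD/AFD SD ratio | Classical F | Kruskal–Wallis | Welch's ANOVA |
|---|---|---|---|
| 1.00 | 5.0% | 5.0% | 4.6–4.9% |
| 1.25 | 6.4–6.8% | 5.4–6.1% | within 4.5–5.3% |
| 1.50 | 8.3–8.4% | 5.8–6.6% | within 4.5–5.3% |
| 2.00 | 11.9–12.3% | 7.2–7.9% | within 4.5–5.3% |

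If BD is wider and HC narrower at once (SDs 1.5 and 0.5), the shifts partly offset: classical F 7.6%, Kruskal–Wallis 4.8%, Welch 4.9%.

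**Cost of Welch if variances are equal.** In one simulated alternative, power was 62.7% with Welch against 63.0% with classical ANOVA.

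**The case against.** The strongest reply is that the text contains no demonstrated error. It does not state equal variances, a pooled error term or any particular pairwise contrast. A condensed article may leave the form of ANOVA and the follow-up comparisons to the full protocol or analysis plan. This stands. The point is therefore a better choice for a named test, and no fault is found in what the article leaves out.

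A reader might infer that the p-values will be wrong. The documents do not support that. No biomarker SD is given, and with equal SDs classical ANOVA holds 5%. AFD is itself mixed (first-episode and recurrent, drug-naive and recently off medication). AFD and BD share the age range, the HAMD-24 threshold and most exclusions. The entry rules bear directly on medication and hypomanic symptoms, but only indirectly on kynurenine or MRI measures.

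A reader might also pool all 480 AFD patients against 100 BD patients in a two-sample test, which gives larger distortions. The plan does not describe that comparison; it splits AFD into two groups.

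Kruskal–Wallis is already named and removes much of the overall distortion, nearly all of it at modest SD ratios. That also stands, but it does not mend pairwise contrasts that use the ANOVA error. Such contrasts are the natural next step after an overall test, although the article does not spell them out.

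Finally, the trial design section calls the study exploratory, and the abstract also plans multivariate analyses to recognise AFD. Both lower the stakes.

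**Conclusion.** The point holds as a conditional, low-severity recommendation. The article names ANOVA for its primary aim on groups of clearly unequal size whose entry rules make unequal spread plausible. If BD is 1.25 to 2 times as variable as AFD, the overall classical F test would run at about 6.4% to 12.0%, and a pooled-error first-episode AFD versus BD contrast at about 8% to 18%. If HC has 0.7 times the AFD SD, the corresponding HC contrast would run at about 2%.

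These figures rest on assumed SDs, an assumed 240/240 AFD split, a 5% level, normal data and full enrolment. Neither the direction nor the presence of the problem can be settled from the article. Welch's method keeps close to its level in every scenario examined, so the choice need not wait for that to be known. The randomised treatment comparison and its sample size are not touched.

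**What to change.** In the additional-analyses section {20b}, for continuous markers, replace the unqualified ANOVA with Welch's ANOVA, followed by Welch (unequal-variance) pairwise comparisons of the AFD groups with BD and with HC. Kruskal–Wallis and chi-square can stay for the data they suit. If the full protocol or analysis plan already specifies this, only the wording needs aligning. No robust-error provision for covariate-adjusted models is needed, because this section plans none.

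The cost is one line of text and a different option in standard software, with no added patients or data. The power loss under equal variances is negligible (62.7% against 63.0% in the case simulated). The article says specimens are to be assayed together once collection is finished, so the change can be made before metabolite results are seen if that step has not yet been taken.
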